## Abstract

**Background:**

Functional abdominal pain (FAP) is not only a highly prevalent disease but also poses a considerable burden on children and their families. Untreated, FAP is highly persistent until adulthood, also leading to an increased risk of psychiatric disorders. Intervention studies underscore the efficacy of cognitive behavioral treatment approaches but are limited in terms of sample size, long-term follow-up data, controls and inclusion of psychosocial outcome data.

**Methods/Design:**

In a multicenter randomized controlled trial, 112 children aged 7 to 12 years who fulfill the Rome III criteria for FAP will be allocated to an established cognitive behavioral training program for children with FAP (n = 56) or to an active control group (focusing on age-appropriate information delivery; n = 56). Randomization occurs centrally, blockwise and is stratified by center. This study is performed in five pediatric gastroenterology outpatient departments. Observer-blind assessments of outcome variables take place four times: pre-, post-, 3- and 12-months post-treatment. Primary outcome is the course of pain intensity and frequency. Secondary endpoints are health-related quality of life, pain-related coping and cognitions, as well as selfefficacy.

**Discussion:**

This confirmatory randomized controlled clinical trial evaluates the efficacy of a cognitive behavioral intervention for children with FAP. By applying an active control group, time and attention processes can be controlled, and long-term follow-up data over the course of one year can be explored.

**Trial registration:**

DRKS00005038 (date: 25 July 2013); NCT02030392 (date: 7 January 2014)

**Electronic supplementary material:**

The online version of this article (doi:10.1186/1745-6215-15-357) contains supplementary material, which is available to authorized users.

## Background

Functional abdominal pain (FAP) is a chronic pain disorder of the gastrointestinal tract without underlying pathological condition [1]. According to the Rome III criteria, functional abdominal pain is specified as functional dyspepsia, irritable bowel syndrome, functional abdominal pain, and functional abdominal pain syndrome [2]. FAP is characterized by recurrent or persistent pain in the abdomen for more than 2 months, with episodes occurring at least once a week [2]. FAP represents, besides headache, the most common pain syndrome in childhood [3], with prevalence rates ranging from 8.3% [3] up to 45% [2]. FAP often leads to functional disability [4], poor school attendance [4] and a number of unnecessary, cost-intensive visits in medical care settings [5]. Children with recurrent episodes of abdominal pain may have a worse quality of life [6] and self-esteem [4] and experience greater anxiety and depression [7, 8]. Untreated, FAP is highly persistent until adulthood, also leading to increased risk of psychiatric disorders (see [9]).

Psychosocial factors in symptom maintenance include inadequate coping styles [10], poor family functioning and overprotective parental behaviors [11]. Catastrophizing plays an especially important role in mediating the relationship between pain and quality of life [6] and moderating the effectiveness of distraction [12].

Systematic reviews and meta-analyses underscore the efficacy of psychological interventions, especially cognitive-behavioral therapy (CBT), for managing pain in childhood and adolescence [13–18]. But only a few treatment studies for pediatric chronic pain consider abdominal pain (3 out of 25; see [16]) and even fewer investigate the emotional functioning of the children [16, 18]. A recent meta-analysis by Sprenger *et al*. [18], including ten studies for the psychological treatment of FAP, showed that interventions obtain a medium-sized effect on pain reduction. These interventions mainly comprised CBT, child-centered or family-based, and relaxation techniques. With respect to functional and emotional outcomes, CBT involving the children alone [19] or parents and children [11, 20–22] proved to be effective in terms of an increase in emotional functioning or in quality of life. Interpretation of studies is limited due to differing definitions of the condition, inadequate control group designs and a lack of assessment of long-term effects [16]. With respect to longer term follow-up and the effectiveness of CBT compared to an active control group, available evidence is limited. Since preparation of this trial, several RCT studies with 12-month follow-up data have been published [23, 24] but with inconsistent results. While Levy *et al*. [11, 23] report a greater decrease in pain symptoms and parental solicitous behavior, as well as greater increase in child’s coping skills in the intervention group compared to the active control group, results of the study by van der Veek *et al*. [24] could not confirm these differences. Comparing a cognitive-behavioral, child-centered intervention and intensive medical care, van der Veek *et al*. [24] found no group differences in pain reduction at post-treatment and at the 12-month follow-up. All secondary outcomes, for example, quality of life, improved equally in both groups.

The current trial builds on the insights gained in two previous studies. For example, in an uncontrolled pilot study with 11 children, we were able to show that children attending a cognitive-behavioral program [20] not only experienced a reduction in pain frequency and intensity, but also an increase in health-related quality of life. A small RCT-study (n = 29; including a waiting list control group) was able to confirm these results with effect sizes ranging from medium to high for a 3-month follow-up period [21, 22].

Taken together, these data suggest that cognitive-behavioral interventions are effective for pain reduction; however little is known about the differential effects on emotional well-being and individual differences in treatment response.

This multicenter trial aims to compare the cognitive-behavioral group intervention with an active control group (age-appropriate educational content), both provided by trained therapists, with respect to a reduction of pain symptoms and an increase in children’s quality of life. The effects are analyzed 3 and 12 months after the end of treatment.

## Methods/Design

### Study design

Stop-FAP is a multicenter, prospective, parallel group, randomized-controlled superiority trial for the evaluation of the efficacy of a cognitive-behavioral group intervention compared to an active control group. Study process from enrollment to follow-up is depicted in Figure 1 (Trial Flow Chart).

**Figure 1 Fig1:**
[figure not shown]
**Trial flow chart.**

#### Study setting

This study is conducted in five study centers, all of which are outpatient clinics for pediatric gastroenterology (Berlin, Darmstadt, Düsseldorf, Hamburg, Ulm). Participating study centers and investigators are fully listed in the German Clinical Trials Register (DRKS00005038) and in the registry of the U.S. National Institutes of Health clinicaltrials.gov (NCT02030392).

### Recruitment

After initiation of the study centers, the 12-month recruitment phase of this ongoing trial started in March 2014. Patients will be recruited consecutively during regular consulting hours. Supplementary recruitment strategies involve active recruitment by information flyers and posters or by informing former patients about the study.

### Participants

Study inclusion follows a stepwise procedure. In the first step we defined eligibility criteria for medical screening as listed below:

#### Medical screening

Inclusion criteria include the following:age 7 to 12 years,Rome III criteria for FAP (that is, abdominal pain at least once per week for at least two months), andunexplained cause for abdominal pain.

Exclusion criteria include the following:insufficient German language skills,mental retardation,physician-ordered medication or therapy (psychological, pharmacological) of gastrointestinal complaints at the screening visit,participation in a clinical trial that may have effects on gastrointestinal symptoms in the preceding 4 weeks,participation in a training program for gastrointestinal complaints in the preceding 6 months, orpresentation of a sibling aged 7 to 12 years suffering from abdominal pain.

The standardized procedure of gastroenterological diagnostics is explained in more detail in the section ‘procedures’ below. In the second step, we defined inclusion criteria for study participation as follows:functional abdominal pain (FAP) presenting as functional dyspepsia, irritable bowel syndrome, functional abdominal pain or functional abdominal pain syndrome (Rome-III Criteria H2a, H2b, H2d, H2d1), andinformed written consent of parent(s) and child.

Exclusion criteria for study participation are as follows:severe internalizing psychiatric disorders with primary treatment indication, orvery limited group skills that are operationalized as severe externalizing disorders.

Sites (n = 5) were selected based on the availability of a pediatric gastroenterological consultation hours and staff experienced in diagnosis and treatment for FAP (for example, certified by the German Society for Pediatric Gastroenterology and Nutrition, GPGE). Eligibility criteria for the selection of trainers (n = 10) were expertise and occupational background for pediatric psychology, chronic pain, child psychotherapy or treatment of children with chronic diseases. All trainers received an intensive training in conducting both interventional and control training (IG and CG) during a mandatory 3-day train-the-trainer seminar.

### Procedures: identification of trial participants

Prior to study inclusion, children will undergo standardized medical and psychological examination to exclude organic gastrointestinal disorders in the first step and psychiatric disorders with primary treatment indication in the second step (see Figure 2). Information about pain symptoms and associated factors (somatoform symptoms and family history of pain) is collected during the screening process by parent questionnaire. We aim to screen n = 450 children.

**Figure 2 Fig2:**
[figure not shown]
**Procedures: identification of trial participants.**

#### Medical screening

Medical screening for exclusion of organic gastrointestinal disorders is standardized across study centers and follows current guidelines [1, 25, 26]. Following a stepwise approach, the physician will clarify red flags by a standardized medical history (related symptoms, fever, blood in the urine, waking up during night, bowel habits, nausea *etcetera*), thorough examination and laboratory diagnostics (that is, blood, urine status, and stool), all of which are obligatory and necessary steps to rule out organic causes of pain such as inflammatory bowel disease [1, 25, 26]. In case of any abnormality, further diagnostics will be conducted accordingly (for example, elimination diet in case of signs of food intolerance). According to the Rome III criteria, in case of no pathological result, a diagnosis of FAP can be established. At this point, information about the trial will be given to the child and parents, and written consent will be obtained by the site investigator.

#### Psychological screening

In the next step, the child will be referred for psychological screening, to rule out primary severe psychological problems associated with abdominal pain. The psychological diagnostics follow a two-step procedure, with a standardized and validated screening questionnaire (SDQ; [27–29]) for all parents of eligible children in the first step. In case of subclinical or clinical scores on the scales for emotional problems, hyperactivity or conduct problems, a structured clinical interview (Kinder-DIPS; [30]) with the parent will be held to verify the reported abnormalities (see [31]), to determine psychological strain, group skills and treatment indication.

Since up to 45% of the FAP children suffer from psychological problems - mainly in the subclinical range [7, 8] - we do include children with subclinical psychological disorders to ensure that we are able to collect a representative study sample. Children with clinically relevant psychiatric symptoms will only be included when FAP is declared to be associated with the highest psychological strain leading to primary treatment indication.

### Intervention and **c**ontrols

Intervention group (IG) and control group (CG) are comparable with regard to group size (3 to 8 children), number and duration of sessions for children (n = 6, 90 min each) and parents (n = 2, 50 min each). Training sessions for children are once a week. In both groups, the intervention period per patient lasts 6 weeks in the study centers, with 2 weeks pre- and postintervention being added for the pain diary. All study centers conduct both treatment approaches.

#### Standardization

Both experimental and control intervention are manualized programs for maximizing standardization and improving protocol adherence.

#### Intervention group - stop the pain with happy pingu

Children and their parents randomized to the IG will participate in the cognitive behavioral self-management program ‘Stop the Pain with Happy Pingu’ [32]. The standardized and manualized intervention addresses the following issues: psychoeducation on FAP, change of negative pain-related thoughts and attention bias, relaxation techniques, coping strategies and self-esteem. Each session includes individual tailoring of content, for example, triggers of pain. A central element of the program is the pain diary that children are asked to keep during the whole intervention in order to increase their self-management skills. Each session is accompanied by regular homework (for example, relaxation) that allows implementing and practicing of the newly learned strategies at home. The child’s experiences can be tackled in the following session.

During the parent group sessions, the parents are primarily informed about the major disease characteristics, the etiology and maintenance of FAP, red flags and nutrition. Main focus of the parental sessions is to coach the parents on how to support their child in his pain management efforts.

#### Control group - educational program

The CG comprises a child-centered educational program [33, 34]. The sessions will include information mainly about the gastrointestinal tract, nutrition and bodily activity. Adverse side effects of this program are not reported [20–22]. In order to measure the course of pain severity continuously, the CG will fill in the pain diary as weekly homework. For ethical reasons, we will inform the parents about the so-called red flags that indicate the need for contacting a medical doctor [1, 25]. All parents will be reassured that there is no serious organic disease present and that the pain of their child is real. There will be no recommendations by the therapist for any food or diet and neither parent nor child will receive a specific training to cope with pain.

#### Treatment integrity and protocol adherence

The quality of the intervention is assured by the standardized manual and a mandatory 3-day train-the-trainer seminar for all the persons conducting the intervention, followed by ongoing supervision via regular telephone calls (once a month) and conferences (every 3 months) and monitoring on the spot.

By checking trainer protocols of sessions, adherence to intervention protocols will be improved by giving feedback to the trainers. In addition, all sessions in both the IG and CG will be recorded by audiotapes. Analysis with respect to protocol violations will be conducted by a trained person blind to treatment allocation.

### Hypotheses

Our primary hypothesis postulates that children in the IG will experience a more pronounced and sustained reduction of the frequency and intensity of abdominal pain than children in the CG.

Secondary hypotheses postulate that after treatment, children in the intervention group - compared to an active control group - will experience (i) higher improvement in health- and pain-related quality of life, (ii) a higher increase in the use of adequate pain-related coping and cognitions, and (iii) a more pronounced improvement in self-efficacy.

Additionally, we assume that children and parents with more pronounced psychosocial strain gain less from treatment than those experiencing low strain.

### Outcome variables

#### Primary outcome measure

The primary outcome is the course of pain frequency and intensity of FAP (composite score) from pretreatment (T1) to post-treatment (T2), 3-month (T3) and 12-month follow-up (T4). Pain symptoms will be assessed via self-report using the pain diary, which has already successfully been implemented in prior trials [20–22]. On 14 consecutive days, children should report intensity of pain on a 10-point visual analog scale. Pain duration and frequency are derived from reports on time spans of when the pain arose.

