### Sample size - power analysis

The calculations rely on the high effect size of our primary outcome (d = 1.09 for the composite pain score; see [21, 22]) and correlation among repeated measures 0.8 (see [20–22]). Since our recent single-site study included a 3-month follow-up and a waiting list control group (instead of an active control group [21, 22]), power analysis for the primary outcome is based conservatively on a medium effect size (f = 0.25; d = 0.6). Independent variables are intervention (2), gender (2), age (2) and site of intervention (5), forming a total of 2^3^*5 = 40 groups.

In the study centers, n = 450 children will be assessed for eligibility and a total number of n = 112 children will be allocated to the trial (n = 56 in IG, n = 56 in CG). We assume a drop-out rate of 20% [cf. 18], resulting n = 112 children to be analyzed in the intention-to-treat analysis (ITT) and n = 90 children for the per protocol analysis (PPA).

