### Primary analysis of the primary endpoints

An analysis of covariance will be performed in the ITT population, comparing the log area under the pain intensity curve from intervention to 12-month follow-up between the two random groups adjusted for the baseline measurements. Length of pain episodes will be analyzed analogously. Frequencies will be analyzed using a Poisson regression model.

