### Confirmatory analysis

In terms of clinical relevance, the composite pain score is the most prominent outcome: a substantial pain reduction is mandatory for treatment efficacy. We therefore apply a hierarchical testing procedure; the number and length of pain episodes will be tested only if there is a significant difference between the treatment groups in the log area under the curve (auc) of pain intensity. These endpoints will be tested to an alpha level of 2.5%; therefore, under this hierarchical design the overall alpha level of the trial will not exceed 5%.

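### The composite pain score declared as the primary outcome has no confirmatory test of its own; the gatekeeping test is on pain intensity.

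*Protocol article*

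**What the plan says.** Five sections of the protocol article bear on which variable decides the trial.

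- **Hypotheses.** The primary hypothesis is that the intervention group will show "a more pronounced and sustained reduction of the frequency and intensity of abdominal pain than children in the CG". Both components are named.
- **Primary outcome measure.** "The primary outcome is the course of pain frequency and intensity of FAP (composite score) from pretreatment (T1") to post-treatment and the 3- and 12-month follow-ups. Intensity is a rating on a visual analog scale over 14 consecutive days. Frequency and duration are derived separately, from the time spans of pain recorded in the diary.
- **Sample size - power analysis.** "The calculations rely on the high effect size of our primary outcome", given as "d = 1.09 for the composite pain score". Because the earlier study had a waiting-list control and only a 3-month follow-up, the "power analysis for the primary outcome is based conservatively on a medium effect size" (f = 0.25; d = 0.6).
- **Primary analysis of the primary endpoints.** The leading analysis is an ANCOVA in the intention-to-treat population, "comparing the log area under the pain intensity curve from intervention to 12-month follow-up between the two random groups", adjusted for baseline. Episode length is handled in the same way and frequency by a Poisson model.
- **Confirmatory analysis.** The section gives the composite score first place in clinical relevance and derives a hierarchy from that. In this hierarchy "the number and length of pain episodes will be tested only if there is a significant difference between the treatment groups" in the log AUC of pain intensity. An alpha level of 2.5% is attached to these endpoints, with an overall level of at most 5%. Sidedness is not stated.

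Under Analysis of secondary outcomes, a mixed model is then planned for the primary as well as the secondary outcome measures.

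**The concern.** The plan names one variable as primary and puts a different one at the gate. The clash is sharpest within the Confirmatory analysis section, where the importance of the composite is the stated reason for a hierarchy that opens with intensity and contains no composite.

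Two things are at stake. First, if the composite and the intensity AUC point in different directions, the document supports two claims about which result is primary, and the choice could be made after the results are seen. Second, if intensity is not significant, frequency loses its confirmatory test although it is half of the primary hypothesis.

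This is not detail that an article leaves to the analysis plan. The article itself states which variable is primary and which is tested first, and no analysis plan could follow both statements.

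**Working it through.** **1. Which variable plays which role**

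| Role | Variable | Section |
|---|---|---|
| Primary hypothesis | frequency and intensity | Hypotheses |
| Declared primary outcome | composite of frequency and intensity | Primary outcome measure |
| Starting point of the power analysis | composite (d = 1.09) | Sample size - power analysis |
| Ranked first in clinical relevance | composite | Confirmatory analysis |
| Gatekeeping test | log AUC of intensity | Primary analysis; Confirmatory analysis |
| Tested after the gate | number and length of episodes | Confirmatory analysis |
| Ungated, non-confirmatory | primary and secondary outcome measures, mixed model | Analysis of secondary outcomes |

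The composite appears in the rows that declare and plan, and in neither confirmatory testing row. The article gives no formula for it.

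**2. Can the intensity AUC stand in for the composite?**

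Suppose a child has pain on k of the 14 diary days, always rated r.

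- If pain-free days score zero, mean intensity is k × r / 14. Halving k halves it, so intensity carries frequency with it.
- If intensity is averaged over painful days only, mean intensity is r. Halving k leaves it unchanged.

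Under the first rule intensity and composite would tend to move together. Under the second, a treatment that acts on frequency alone would not shift the gate. The article does not say which rule applies.

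**3. Does the sample size settle the matter?**

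The stated figures are 112 allocated (56 per arm) and 90 for the per protocol analysis. The section gives no power, alpha or sidedness, so 112 cannot be reproduced from stated inputs alone. Assuming a two-sided 5% level and 80% power, with n per arm = 2(z₁₋α/₂ + z₁₋β)² / d²:

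- d = 0.6: 2 × (1.96 + 0.84)² / 0.36, which rounds up to 44 per arm, or 88 in total; 88 / 0.8 = 110. These are within 2 of the stated 90 and 112.
- d = 0.5: 63 per arm, or 126 in total before drop-out. This value is included because, for two equal groups, d = 2f, so f = 0.25 is d = 0.5 and not 0.6.

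Two-sided power of a simple two-group comparison:

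| Assumed d | Level | 56 per arm | 45 per arm |
|---|---|---|---|
| 0.6 | 5% | 0.89 | 0.81 |
| 0.6 | 2.5% | 0.83 | 0.73 |
| 0.5 | 5% | 0.75 | 0.66 |
| 0.5 | 2.5% | 0.66 | 0.55 |

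Nothing in these figures is specific to the composite or to intensity. They fit a generic two-group comparison of any continuous variable with that effect size. They neither support nor refute the point, which rests on the text. They do show that the level chosen for the gate matters: moving from 5% to 2.5% costs 6 to 11 percentage points of power (for example 0.89 to 0.83, and 0.66 to 0.55).

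**The case against.** The strongest reply is that both components of the primary outcome are in the confirmatory plan. The analysis section speaks of primary endpoints in the plural and gives each a model, and the hierarchy includes the number of episodes. The mixed model has no gate, so frequency is analysed whatever happens to intensity. This stands. A reader might infer that the declared primary outcome, or at least frequency, is never tested; the documents do not support that. What is missing is a confirmatory test of the composite itself, and an unconditional one for frequency.

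A second reply is that the authors may regard the intensity AUC as the working form of the composite, since the confirmatory section moves directly from one to the other. With pain-free days scored zero that would be reasonable. It remains inference: the outcome section defines intensity and frequency separately, and the analysis section models frequency on its own. For the same reason, a reader might infer that a treatment which reduces only frequency must fail at the gate. That holds under one scoring rule and not under the other, so it is a possibility and not a finding.

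A third reply concerns power. A reader might infer that the trial is powered for the composite and underpowered for intensity. Only d = 1.09 is a composite estimate; the planning value is a conventional medium effect. No power deficit follows.

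Episode length in the hierarchy might also be questioned, as it is part of neither the hypothesis nor the composite. But duration is listed among the diary measures in the primary outcome section, and length is tested only after the gate, so it cannot decide the trial.

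**Conclusion.** The point holds as an inconsistency over which variable decides the trial. The composite is declared primary, starts the power analysis and is ranked first in clinical relevance, yet has no confirmatory test of its own. The gate is the log AUC of intensity, and frequency has a confirmatory test only if that gate is passed.

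The size cannot be put as a number. The chance that the two variables disagree depends on the unstated scoring of pain-free days and on the undefined composite. The power of the gatekeeping test cannot be computed either, because no effect size or standard deviation is given for intensity or its log AUC; using d = 0.5 to 0.6 for it is an assumption.

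It should be corrected all the same, because it determines which result counts as the trial's answer and the sections cannot all be followed as written.

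**What to change.** Make the sections Primary outcome measure, Sample size - power analysis, Primary analysis of the primary endpoints and Confirmatory analysis name one primary variable. There are two consistent ways.

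1. **Keep the composite.** Define the score, including how pain-free days enter it. Put its baseline-adjusted AUC at the gate, on the scale that the plan specifies, and test intensity, number and length of episodes after it. The planned 112 can stay.
2. **Keep intensity.** Declare the log AUC of intensity as the primary outcome in the Abstract, Hypotheses, Primary outcome measure and Confirmatory analysis, and state how pain-free days are scored. In the sample size section, say that the planning effect size is an assumption for that variable.

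In either case, state the alpha level and sidedness of the gate together with the endpoint. The present wording gives 2.5% without sidedness and does not make clear whether that level applies to the gate or only to the tests after it.

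The cost is wording in the protocol and analysis plan. The diary already supplies both components, so no new data are needed. The article describes the trial as still recruiting and places regular unblinding after the last 12-month data are entered, so the change can be made, dated and justified before anyone sees results by arm.
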